### Study design

The ValvEx-trial is a randomized controlled trial (RCT). It is performed in two centers (the university hospital of Gießen and the university hospital of Marburg). The trial examines the impact of a brief preoperative psychological intervention that aims to optimize expectations (EXPECT) in addition to standard of care compared to standard of care (SOC) only in heart valve patients. The randomization ratio is balanced (1:1). Assessments take place on the day before surgery in the hospital (Baseline, T0a), on the evening before surgery, after the intervention (EXPECT)/after waiting time in the evening of hospital admission (SOC) (T0b), 4 to 6 days after surgery (T1) and 3 months after surgery (T2). Figure 1 shows the calculated study flow-chart, including the participants’ targeted count for each measurement.

**FIGURE 1 F1:**
[figure not shown]
Study flow chart.

### Sample size and study power

In PSY-HEART I, a large effect (*d* = 0.8) was detected relating to the pre-post comparison of the primary outcome (illness-related disability) in the EXPECT and SOC group (21). Since the intervention is shortened to one preoperative session (and two additional booster sessions after surgery) in ValvEx, a small to medium effect is expected (*d* = 0.2–0.5). Given a power (1 − β) of 0.8 and a significance level of *p* = 0.05, a sample size of *N* = 74 is required to detect the described effect (*d* = 0.3, *f* = 0.15). In due consideration of a drop-out rate amounting to 20% for refusals and terminations of treatment, a recruitment aim of *N* = 88 is intended.

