In the context of the PSY-HEART trial, Rief and colleagues addressed this issue and developed a preoperative intervention (EXPECT) to optimize the patients’ expectations before undergoing coronary artery bypass graft (CABG) surgery (21, 26).

Medical treatments combine both specific factors (e.g., active pharmacological ingredient of a drug or a surgical procedure) and unspecific factors (e.g., patients’ expectations of the treatment outcome), while the unspecific factors of treatments are considered crucial for placebo effects. The EXPECT intervention was based on expectations as one of the most important placebo mechanisms driving placebo effects (27). Placebo effects not only influence subjective dimensions (e.g., quality of life) but have been shown to contribute substantially to surgery outcomes and immune parameters (28). The PSY-HEART-trial indicated effects of the intervention on expectations and depressive symptoms: Patients in the intervention group developed higher personal control expectations, more realistic expectations of the duration of disease, and, in some cases, more positive disability expectations compared with standard of care (SOC) (29). The EXPECT intervention consisted of five appointments: two in-person sessions (approx. 40–60 min) and two telephone calls (approx. 15–20 min) 3–10 days before surgery and one booster telephone call 6 weeks after CABG surgery (30). The positive-realistic expectations developed in the intervention were associated with a better course of treatment 6 months after surgery: The results showed a lower illness-related disability [Cohen’s *d* = 0.75; interpretation of the effect sizes: Cohen’s *d*_small effect size_ = 0.2, Cohen’s *d*_medium effect size_ = 0.5, Cohen’s *d*_large effect size_ = 0.8 (31)], a shorter hospital stay (Cohen’s *d* = 0.46), an earlier return to work (Cohen’s *d* = 0.42), and a higher quality of life (Cohen’s *d* = 0.50) (21, 32). The intervention also influenced physiological parameters such as stress/adrenaline (Cohen’s *d* = 0.34) and immunological parameters (Cohen’s *d*_interleukin–8_ = 0.47, Cohen’s *d*_interleukin–6_ = 0.37) positively (21, 33, 34). However, in the PSY-HEART I trial, almost half of the eligible patients (*n* = 99, 44%) declined to participate in the trial because of difficulties traveling to the additional study appointments, additional time required (four measurement time points and if applicable, approx. 140 min for the intervention), or lack of interest. The additional prehospital intervention appointments and time investment hindered patients’ participation in the trial.

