### Hypotheses

The study aims to examine if a brief preoperative psychological intervention (EXPECT) compared to standard of care (SOC) leads to a lower level of subjectively perceived illness disability 3 months after surgery. Therefore, the hypothesis μ_EXPECT_ = μ_SOC_ (μ = mean change from baseline) is tested with an α-level of 0.05 (two-sided).

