### Data analysis

For examination of the primary hypothesis (H0: μ_EXPECT_ = μ_SOC_; H1: μ_EXPECT_ ≠ μ_SOC_), the illness-related disability 3 months after surgery will be analyzed using linear mixed models (baseline-adjusted, patients nested in operation type nested in centers). Main effects for group, time, and group x time will be calculated with primary focus on the difference in treatment effect (difference in mean change between baseline and 3-months follow-up between EXPECT and SOC). In doing so, a fixed significance level of α = 0.05 will be used, and Intention-to-treat-analysis (ITT) will be conducted. The reasons for upcoming missings will be analyzed, and robust maximum likelihood estimation procedures will be applied.

95% confidence intervals will be calculated for the estimation of differences in mean values. Relevant factors such as strata (center, surgery method), baseline characteristics (e.g., age, gender, level of baseline depression and anxiety score) or potential confounding (e.g., differences in interventionists) may also be considered in secondary analyses. The same procedure will be applied for secondary outcomes.

In the PSY-HEART I study, the EXPECT intervention has been shown to have partially different effects for different severities of some outcomes, for example due to the fact that the EXPECT intervention significantly decreased depressive symptoms at 6 months follow-up for patients with high baseline depressive symptoms, but not for patients with low baseline depressive symptoms (60). Therefore, covariate/moderator analyses will be conducted to examine whether the intervention is more effective for specific subgroups in terms of “what works best for whom”.

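### With 74 evaluable patients, power for d = 0.3 on the stated primary contrast is well below the claimed 80%: about 25–31% at an assumed correlation of 0.5, and at most 56% for correlations of 0.3–0.8

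*Protocol article*

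**What the plan says.** In the protocol article, Sample size and study power sets the expected effect for the shortened intervention: "a small to medium effect is expected (*d* = 0.2–0.5"). The requirement that follows reads "a sample size of *N* = 74 is required to detect the described effect (*d* = 0.3, *f* = 0.15"), and the error rates behind it are 80% power and a 0.05 significance level. The section names no statistical test, no number of measurements and no correlation between them.

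The primary test is fixed elsewhere. Under Hypotheses, equality of the two group means is the null hypothesis ("μ = mean change from baseline) is tested with an α-level of 0.05 (two-sided"). Data analysis specifies a baseline-adjusted linear mixed model with "primary focus on the difference in treatment effect (difference in mean change between baseline and 3-months follow-up between EXPECT and SOC"). Under Study design, "The randomization ratio is balanced (1:1"). Table 2 schedules the PDI at three assessments: T0a, T1 and T2.

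**The concern.** For two equal groups, d = 0.3 is a fairly small difference, and a total of 74 is far below what a two-group comparison of that size usually needs. The pairing of d = 0.3 with f = 0.15 is the relation f = d/2. That relation is correct for a main effect between two groups, but not for a group-by-time interaction.

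The planned power is what readers use to interpret a non-significant primary result. If the trial is described as having 80% power for d = 0.3 and has much less, such a result could be taken as evidence against the shortened intervention when the data cannot exclude the effect the plan expects. The Introduction makes implementation in routine care depend on whether this trial shows a benefit.

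**Working it through.** **Inputs from the article.** Two-sided α = 0.05 (Hypotheses); power 0.80, d = 0.3, f = 0.15 and N = 74 (Sample size and study power); 1:1 allocation (Study design); contrast = group difference in change from baseline to 3 months, baseline-adjusted (Data analysis); PDI at three time points (Table 2).

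**Assumption.** The baseline/follow-up correlation ρ is not given. I use 0.5 and show 0.3–0.8.

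**1. Where 74 can come from.** A two-sample t test at d = 0.3 needs a total of 352 two-sided (278 one-sided), so it is not the source. For a repeated-measures group-by-time interaction with 2 groups and m measurements:

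λ = f²·N·m/(1 − ρ), df = (m − 1) and (N − 2)(m − 1).

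With f = 0.15, m = 3, ρ = 0.5 and N = 74: λ = 0.0225 × 74 × 3 / 0.5 = 9.99, df = 2 and 144, power 80.6%. At N = 72 power is 79.5%, so 74 is the smallest balanced total. At ρ = 0.5, m = 2 gives 90 and m = 4 gives 62.

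**2. What f = 0.15 means in that test.** If the group differences over time are g₁,…,g_m, the interaction f in SD units is √(mean of [(g_j − ḡ)/2]²).

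| Pattern at T0a, T1, T2 | f | f when d = 0.3 | d when f = 0.15 |
|---|---|---|---|
| 0, 0, d | 0.236d | 0.071 | 0.64 |
| 0, d/2, d | 0.204d | 0.061 | 0.73 |
| 0, d, d | 0.236d | 0.071 | 0.64 |

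So f = 0.15 stands for a 3-month difference of 0.64–0.73 SD. If d is really 0.3, even the interaction test has only 19–24% power at N = 74.

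**3. Power for the stated contrast.** Noncentral t with 72 df and noncentrality δ√74/2, where δ = d/√(2(1 − ρ)) for the change score and δ = d/√(1 − ρ²) for baseline adjustment, with d on the raw-score SD. At ρ = 0.5:

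- change score: δ = 0.3/√1 = 0.300, noncentrality 1.29, power 24.7%;
- baseline-adjusted: δ = 0.3/√0.75 = 0.346, noncentrality 1.49, power 31.2%.

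| ρ | Change score | Baseline-adjusted |
|---|---|---|
| 0.3 | 19% | 27% |
| 0.5 | 25% | 31% |
| 0.6 | 30% | 36% |
| 0.7 | 38% | 43% |
| 0.8 | 52% | 56% |

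If d is instead standardised by the SD of change, change-score power is 24.7% at any ρ. If all 88 recruited patients are analysed, the figures at ρ = 0.5 are 28.5% and 36.2%.

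**4. What 80% would require.** At N = 74 the t test reaches 80% at δ = 0.66.

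- Correlation needed for d = 0.3: 1 − (0.3/0.66)²/2 ≈ 0.90 (change score), or √(1 − (0.3/0.66)²) ≈ 0.89 (baseline-adjusted).
- Total N needed at ρ = 0.5: 352 or 264.
- Detectable difference at N = 74 and ρ = 0.5: 0.66 × √1 = 0.66 SD, or 0.66 × √0.75 = 0.57 SD.

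**The case against.** The best counter-argument is that the derivation of 74 is a guess. The article names no test, and other inputs also give 74: the interaction test with f = 0.15 yields it at m = 2 with ρ = 0.59 and at m = 4 with ρ = 0.41. That stands. A reader might infer that 74 can only be a three-time-point calculation, or that a 2-df interaction was powered in place of the 1-df primary contrast. The article supports neither; with two measurements the interaction is the change contrast itself. Three measurements with ρ = 0.5 is only the most natural match to Table 2. The shortfall in step 3 does not depend on it.

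Second, 25–31% rests on ρ = 0.5, which the article does not supply, and the scale of d is undefined. This also stands, so the range must be quoted with the figure. No correlation from 0.3 to 0.8 brings power above 56%.

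Third, a reader might infer that the trial will probably miss an effect of the size it expects, or that its detectable effect lies above the whole expected range. Neither follows. At d = 0.5, the top of that range, power at N = 74 is 56% or 69% for ρ = 0.5, and 78% or 84% for ρ = 0.7. Baseline-adjusted power therefore already exceeds 80% at d = 0.5 when ρ = 0.7.

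Finally, the article already plans 95% confidence intervals and nowhere says that a null result will be read as no effect. Misreading is a risk, not something the plan commits to.

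**Conclusion.** The stated power is wrong as written, and nothing else in the article corrects it. For d = 0.3, the shortfall against 80% is about 49 to 55 percentage points at ρ = 0.5 (80 − 31.2 and 80 − 24.7) and at least 24 points anywhere in 0.3–0.8 (80 − 56). This rests on 74 evaluable patients, a two-sided 0.05 test and d on the raw-score SD.

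The explanation, that f = d/2 was used as an interaction effect, is likely but inferred. On that reading the calculation was really for an effect near the d = 0.75 that the Introduction reports for the longer intervention, although the sample-size section expects less because the intervention was shortened.

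If the true effect is about 0.3 or smaller, a non-significant result is more likely than not at correlations up to about 0.7. That statement should not be extended to the upper part of the expected range.

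**What to change.** Keep the sample size. Delete the statement that 74 patients detect d = 0.3 with 80% power and replace it with a figure that carries its assumption, for example:

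> With 74 evaluable patients the trial has 80% power for a between-group difference in PDI change of about 0.57 SD (baseline-adjusted) to 0.66 SD (change score), assuming a baseline/follow-up correlation of 0.5. Power for d = 0.3 is about 25–31% under that assumption (19–56% for correlations of 0.3–0.8).

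If the authors have a correlation for the PDI, use it and state its source. Also say which SD standardises d, and name the test behind the calculation. Optionally, add that a non-significant result will be read through the 95% confidence interval already planned.

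The cost is a change of wording and a less favourable stated power. No further patients are needed, and the analysis does not change.

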**Materials and analysis:**

In two German university hospitals, *N* = 88 heart valve patients who undergo heart surgery are randomized into two groups [standard of care (SOC) vs. standard of care plus interventional expectation manipulation (SOC and EXPECT)] after baseline assessment. Patients in the EXPECT group additionally to standard of care participate in the preoperative psychological intervention (30–40 min), focusing on optimizing expectations and have two booster-telephone calls (4 and 8 weeks after the surgery, approx. 15 min). Both groups have assessments again on the evening before the surgery, 4 to 6 days, and 3 months after the surgery.

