	Masking: medical staff.
	Assignment: two-arm.
	Randomization: balanced block randomization (8:8); prestratifications: study center (Marburg or Giessen); and scheduled type of surgery (minimally invasive or open heart surgery).
	Primary purpose: improvement of the recovery process afer heart valve surgery.
Date of first enrolment	June 2020.
Target sample size	88.
Recruitment status	Recruiting.
Primary outcome(s)	Illness-related disability 3 months after surgery.
Key secondary outcomes	Health-related quality of life, expectations, illness beliefs, anxiety, depression, rehospitalization, length of hospital stay.
Ethics review	Status: Approved.
	1. Ethics Committee of the Department of Medicine of the Philipps University of Marburg (AZ 46/20; 2020-05-20).
	2. Ethics Committee of the Department of Medicine of the University of Giessen (AZ 131/20; 2020-08-17).
Completion date	Remaining.
Summary results	Remaining.
IPD sharing statement	Data can be requested on demand.

World Health Organization trial registration data set version 1.3.1.

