## Ethics and dissemination

The Ethics Committees of the Department of Medicine of the Philipps University of Marburg (AZ 46/20; 2020-05-20) and the Department of Medicine of the University of Giessen (AZ 131/20; 2020-08-17) approved the study protocol, the patient information, and the informed consent (version 1, issue date: 2020-03-09). The study protocol and implementation are in conformity with the principles of the Declaration of Helsinki. The SPIRIT reporting guidelines were applied (61). All patients receive the standard medical procedure. Any protocol modifications must be confirmed by amendments in consultation with both Ethics Committees and will be communicated to investigators and participants. The written patient information and the patient consent can be found in the appendix.

In agreement with the Ethics Committees, no external data monitoring commitee and audits were necessary. Study performance was continuously monitored by the study coordinators. No interim analyses will be performed. Possible conspicuities regarding suicidality (PHQ-9) will be checked and communicated to the study centers if they occur. Additional conversations will be conducted with patients whenever there is a need. Patients will be informed that they can contact the study management with concerns at any time during and also after the study period. The study coordinators will terminate the trial when the target sample size is reached.

If patients decide to decline participation at individual measurement time points, they will still be interviewed at the other measurement time points. Similarly, patients in the EXPECT condition may decline to participate in individual conversations in the intervention. In this case, they continue participation without any changes. Any deviations from the study protocol will be recorded. Adverse events will be documented by the study investigators and will be reported to the principal investigators immediately. The principal investigators will evaluate the adverse event and advise how to deal with it. These will be reported in publications.

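### The required 74, the 20% drop-out and the target of 88 do not fit together: 88 randomised with 20% loss leaves about 70

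*Protocol article*

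**What the plan says.** All the figures stand in the section Sample size and study power of the protocol article.

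- Conditions: "Given a power (1 − β) of 0.8 and a significance level of *p* = 0.05".
- Required number: "a sample size of *N* = 74 is required to detect the described effect (*d* = 0.3, *f* = 0.15").
- Allowance for loss: a "drop-out rate amounting to 20% for refusals and terminations of treatment, a recruitment aim of *N* = 88 is intended".

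Other sections confirm what 88 refers to. The abstract gives N = 88 and says that "heart valve patients who undergo heart surgery are randomized into two groups" after the baseline assessment. Table 1 repeats 88 as the target sample size. So 88 counts patients randomised, not patients approached or analysed.

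The section Ethics and dissemination makes 88 the end point of recruitment: "The study coordinators will terminate the trial when the target sample size is reached". The same section says that no interim analyses will be performed.

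**The concern.** An allowance for drop-out should leave the required number once the stated loss has occurred. Here the margin is 88 − 74 = 14 patients, and 20% of 88 is 17.6. The allowance is therefore smaller than the loss it is meant to absorb. A reader of the section will believe that power 0.8 survives 20% attrition, and on the article's own figures it does not. Recruitment ends at 88, and the visible text describes no replacement of patients who drop out.

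**Working it through.** **Inputs**

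- Required number 74, drop-out 20%, target 88, power 0.8, f = 0.15: Sample size and study power.
- Two-sided α of 0.05: Hypotheses.
- 1:1 allocation: Study design.
- Three PDI measurements (T0a, T1, T2): Table 2. The article does not say that its calculation used three.
- Correlation between measurements: not stated. It is assumed to be 0.5, with a range of 0.3 to 0.7.

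**Step 1. Where 88 could come from.**

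- n × (1 + d) = 74 × 1.20 = 88.8. Cut to a whole number this is 88; rounded up it is 89.
- n / (1 − d) = 74 / 0.80 = 92.5, so 93, or 94 for equal arms.

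The first form comes within one patient of the stated target. The second is 5 away from it.

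**Step 2. What 88 delivers at the stated loss.** 88 × (1 − 0.20) = 70.4, about 70 patients, which is 4 fewer than 74.

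**Step 3. What loss 88 can bear.** 1 − 74/88 = 14/88 = 15.9%.

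**Step 4. Effect on power.** A model is needed that returns the plan's 74. Take the repeated-measures group-by-time F test with k = 2 groups and m = 3 measurements:

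- noncentrality λ = f² × N × m / (1 − ρ)
- degrees of freedom (k − 1)(m − 1) = 2 and (N − k)(m − 1)

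With ρ = 0.5, the smallest even N with power of at least 0.80 is 74, so the plan's figure is reproduced. At N = 74, λ = 0.0225 × 74 × 3 / 0.5 = 9.99 on 2 and 144 degrees of freedom. At N = 70, λ = 9.45 on 2 and 136.

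| Assumed correlation | Power at N = 74 | Power at N = 70 | Loss |
|---|---|---|---|
| 0.3 | 0.655 | 0.628 | 0.027 |
| 0.5 | 0.806 | 0.782 | 0.024 |
| 0.7 | 0.960 | 0.950 | 0.010 |

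Only the row for 0.5 returns 74 as the required number. With three measurements, the same test needs 102 patients at correlation 0.3 and 46 at 0.7. The other rows show that the cost of the mismatch stays at about 1 to 3 percentage points across the range.

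**The case against.** **The method is not shown.** A reader might infer that the plan multiplied by 1.2 where it should have divided by 0.8. The article gives no formula, and 88.8 would normally round to 89, so even that account needs a cut downwards. This objection stands: the multiplication is only the likeliest reconstruction. The mismatch does not depend on it, because 80% of 88 is below 74 however 88 was reached.

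**Drop-out is not the same as a missing outcome.** A reader might also infer that exactly 70 patients will be available for analysis. The article does not support that.

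- The 20% covers refusals and terminations of treatment, not missing 3-month PDI as such.
- Under Ethics and dissemination, patients who skip one measurement are still assessed at the others, and EXPECT patients who decline individual conversations stay in the trial.
- Under Data analysis, the comparison is intention-to-treat with a linear mixed model and maximum likelihood, so partial data contribute.

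This also stands, and it makes 70 the pessimistic count under the stated 20%. It does not rescue the sentence, because the sample-size section itself treats the 20% as a loss to be compensated and 88 does not compensate it. Nor can refusals be read as refusals before enrolment, since 88 is the number randomised.

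**Figure 1 is not visible.** Study design says that it gives the targeted count at each measurement. It might show the number expected at 3 months, so the statement that nothing makes up the shortfall is limited to the text that can be read.

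**Seriousness.** A reader might take this slip as a main reason to doubt the trial's power. About 4 patients and 1 to 3 percentage points do not support that. Whether 74 is itself adequate for the stated effect is a separate question, and 74 is taken as given here.

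**Conclusion.** The point holds as an inconsistency among three stated figures. With 88 randomised and 20% lost, about 70 remain rather than 74. Keeping 74 would need 93 (94 for equal arms), and 88 tolerates at most 15.9% loss. These results need only the article's own numbers and the reading of a drop-out rate as a share of those randomised.

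The consequence is small. Power falls from 0.806 to 0.782 if the calculation was a repeated-measures interaction test with three measurements and correlation 0.5, neither of which the article states as an input. The fall is smaller still if some patients counted as drop-outs supply the 3-month PDI or partial data. The sentence is wrong as written and should be corrected, but the design and the analysis are not undermined by it.

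**What to change.** Keep N = 88 and rewrite the last sentence of Sample size and study power in one of two ways:

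- *88 randomised patients allow for a loss of about 16% while retaining the required 74*; or
- *88 randomised patients with a loss of 20% leave about 70*, followed by the power at 70 on the model that produced 74.

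With the second wording, name that model and declare its number of measurements and assumed correlation. If the model is the one reconstructed above, the power to report is 0.782 at correlation 0.5. Detectable-effect figures do not belong in this correction, because they turn on the separate question of the effect size.

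The cost is one sentence and a slightly less favourable figure. No patients are added, and conduct and analysis do not change.
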